## Abstract

**Background:**

Work-related stress is associated with a variety of mental and emotional problems and can lead to substantial economic costs due to lost productivity, absenteeism or the inability to work. There is a considerable amount of evidence on the effectiveness of traditional face-to-face stress-management interventions for employees; however, they are often costly, time-consuming, and characterized by a high access threshold. Web-based interventions may overcome some of these problems yet the evidence in this field is scarce. This paper describes the protocol for a study that will examine the efficacy and cost-effectiveness of a web-based guided stress-management training which is based on problem solving and emotion regulation and aimed at reducing stress in adult employees.

**Methods:**

The study will target stressed employees aged 18 and older. A randomized controlled trial (RCT) design will be applied. Based on a power calculation of d=.35 (1-β of 80%, α = .05), 264 participants will be recruited and randomly assigned to either the intervention group or a six-month waitlist control group. Inclusion criteria include an elevated stress level (Cohen’s Perceived Stress Scale-10 ≥ 22) and current employment. Exclusion criteria include risk of suicide or previously diagnosed psychosis or dissociative symptoms. The primary outcome will be perceived stress, and secondary outcomes include depression and anxiety. Data will be collected at baseline and seven weeks and six months after randomization. An extended follow up at 12 months is planned for the intervention group. Moreover, a cost-effectiveness analysis will be conducted from a societal perspective and will include both direct and indirect health care costs. Data will be analyzed on an intention-to-treat basis and per protocol.

**Discussion:**

The substantial negative consequences of work-related stress emphasize the necessity for effective stress-management trainings. If the proposed internet intervention proves to be (cost-) effective, a preventative, economical stress-management tool will be conceivable. The strengths and limitations of the present study are discussed.

**Trial registration:**

German Register of Clinical Studies (DRKS): DRKS00004749

## Background

Stress at work is known to almost every employee. Shorter periods of work-related stress elicit acute stress reactions but are not hazardous to health and can even enhance the workers’ ability to meet challenges at work. However, if stress passes into a chronic state of tension, serious negative health consequences can result [1-3].

The prevalence rate of stress in employees varies considerably depending on several factors, such as the definition of stress, the measurement that is used or the occupation of the workers. A European survey of 21,703 workers showed that 28% of workers experience work-related stress, and the percentages range from 17% in elementary occupations to 40% in professionals [4].

A meta-analysis found that job strain and effort-reward imbalances produce consistent increases in the risks for common mental disorders [3]. Work stress may precipitate diagnosable depression and anxiety in workers who were previously healthy [5]. Furthermore, sleep disturbances are a common negative consequence of stress [6]. Moreover, work-related stress can have adverse effects on a societal level due to sickness leave [7] and work disability [8]. According to the American Institute of Stress, the cost estimates of job stress amount to “over $300 billion annually due to increased absenteeism, employee turnover, diminished productivity, medical, legal, and insurance expenses, and workers' compensation payments.” [9]

A variety of effective traditional occupational stress-management trainings are available [10,11]. An extensive meta-analysis [10] showed that the effectiveness of these trainings varies depending on the type of intervention and outcome measure applied. The efficacy of these interventions ranges from d=.11 (the effect of relaxation on depression) to d=.70 (the effect of cognitive behavioral therapy on anxiety) and the overall effect size across all studies is d=.34. However, occupational stress-management interventions are often taught to only a small group of people who are guided by an instructor and these interventions take place at a specific location [11].

Compared to face-to-face interventions, web-based guided self-help interventions offer the advantages of being independent of time, location and group. Furthermore, web-based guided self-help interventions have shown moderate to large effect sizes in numerous studies of, for example, depression and anxiety [12]. A number of randomized controlled trials on web-based stress-management interventions have been performed, including studies on general populations of people with stress-related complaints [13-15] or work-related stress [16], college students [17], women [18], families [19,20], and individuals with burnout symptoms [21]. Thereby, the effect sizes for studies that use stress as an outcome measure vary from non-significant [17] to moderate (d = .60) [16]. However, only few studies have investigated the potential of web-based stress-management interventions in employees [22-27]. These studies of employees apply a wide range of outcome measures, including stress, depression, anxiety, and physiological measurements. With regard to the respective outcome measure, the results again vary between non-significant for stress [23,26] to moderate for depression [24].

To date, the cost-effectiveness of worksite mental health interventions has been studied only in a limited number of trials [28]. A recent systematic review [28] found that these interventions might be cost-effective; however, more high-quality economic evaluations are needed to draw firm conclusions. Data on cost-effectiveness has not been presented in any of the afore-mentioned studies on web-based stress-management for employees. For web-based interventions, studies currently investigate the cost-effectiveness of mental health interventions for workers, including studies of a workers’ health surveillance mental module [29] and a guided self-help course for workers with depressive symptoms [30]. However, to the best of our knowledge, there are no studies with full economic evaluations of the cost-effectiveness of web-based stress-management training for employees.

The theoretical basis of web-based interventions for stress is diverse and ranges from cognitive behavioral methods [16,22,24,27], mindfulness [15,31], problem solving [13], social cognitive theory [23,32] to health behavior change theory [23]. Surprisingly however, there are currently no web-based interventions with content based on specific stress models, such as the job-demand control model [33], the effort-reward imbalance model [34] or more generic models of stress, such as the transactional model of stress [35]. Lazarus’ transactional model of stress [35] can be applied to working contexts and other life areas. This model identifies two strategies of coping with stressors: problem- and emotion-oriented coping. Some web-based stress-management interventions have already included problem solving as part of their intervention content [14,24,32,36] or as stand-alone interventions [13]. However, web-based stress-management interventions employing a combination of problem- and emotion-oriented coping methods currently do not exist.

At work, people often must not only cope with difficult situations and solve problems but also face challenging emotions that arise from these situations. Deficits in emotion regulation skills are an important factor in the development and maintenance of a broad range of mental disorders, such as depression [37-39] and anxiety [40]. As deficits in the ability to adaptively cope with difficult emotions are related to various mental health problems [41], the usage of emotion regulation techniques in a low-threshold web-based stress-management training to reduce symptoms of distress appears promising.

The available web-based stress-management interventions cover a wide range of primary treatment components, including several cognitive behavioral methods [16,21,22,24]. In addition, some interventions focus not only on stress but also on health behavior problems such as alcohol abuse [22,23] and unhealthy diets [23]. A meta-analysis [11] found that occupational stress-management interventions that focus on fewer treatment components are more effective than interventions that include several components. The authors of this meta-analysis found combined effect sizes of d=.64 and d=.61 for the effectiveness of interventions with one or two treatment components, respectively; and treatments with four or more components yielded a smaller effect size of d=.27 [11]. Thus, it appears promising to opt for fewer intervention components in stress-management interventions.

### Aims of the study and hypotheses

In this study, we will investigate the efficacy and cost-effectiveness of a newly developed web-based stress-management training for stressed employees that is based on problem solving and emotion regulation. As a theoretical basis we have followed the transactional stress model of Richard Lazarus [35]. We hypothesize that participants in the intervention group will show a greater reduction in the primary outcome perceived stress from pre-test to post-test compared to a waitlist control group, and that this effect will be maintained over six months. We will conduct cost-effectiveness and cost-utility analyses from a societal perspective and hypothesize that the intervention will be cost-effective. Furthermore, explorative moderator analyses will be conducted.

## Methods

### Study design

A randomized controlled trial with two conditions will be conducted. The intervention group will receive the web-based stress-management training “GET.ON Stress” and the control group will obtain access to this intervention after 6 months (see Figure 1). There will be no restriction with regard to the use of medication or other treatment as usual (TAU) (e.g., psychotherapy) in either of the groups. To control for potential confounding effects, TAU will be monitored.

**Figure 1 F1:**
[figure not shown]
Study flow chart.

### Inclusion and exclusion criteria

The target group will consist of stressed employees from the general working population aged 18 years or older. Inclusion criteria will include current employment and a distinct level of perceived stress as indicated by scores of 22 and above on the Perceived Stress Scale (PSS-10). This cut-off was chosen to select participants with a marked level of subjective stress as identified by one standard deviation (SD = 6.2) above the mean (PSS-10 = 15.3) in a large working population [42]. Applicants with an elevated risk of suicide (Beck Suicide Item > 1) and applicants that self-report having been diagnosed with psychosis or dissociative symptoms in the past will be excluded. For applicants that are at risk for suicide we follow a standardized procedure. These applicants will be advised to seek help via their general practitioner, the local psychiatric emergency room or an official emergency number, and the relevant information and telephone numbers will be provided by email.

### Procedure

Participants will be recruited from the general working population via mass media (e.g., newspaper articles, television) between March and October 2013. Moreover, a major health insurance company (BARMER GEK) will support the recruitment process within their occupational health management program. On an open access website (http://www.geton-training.de) the interested people will be able to sign up to participate with an email-address. Applicants will receive further informational material concerning the study conditions and the training and will be asked to provide an email-address and a first and last name (which can be pseudonyms if desired) to participate. Afterwards, a link to the screening questionnaire will be sent. Applicants who are eligible for participation will be required to provide their informed consent and fill out the online baseline questionnaire. Subsequently, these participants will be randomly allocated to either the intervention or the control group. Participants will be informed of the outcome of the randomization and participants in the intervention group will receive immediate access to the GET.ON Stress training. Assessments will be scheduled at seven weeks and six months after randomization for both groups. However, the participants in the control group will receive the login data required to complete the training six months later than the intervention group. An extended follow-up for the intervention group is scheduled 12 months post-randomization.

### Randomization

The randomization will be carried out by an independent researcher using a web-based randomization program (randomisation.eu) that will be set to allocate participants (N=264) into each group at a ratio of 1:1.

### Sample size

We aim to include 264 participants to produce a statistically relevant effect size of d = .35, a power (1-β) of 80% and an alpha of .05 (two-tailed test) for intention-to-treat analysis using PASS 12. A comprehensive meta-analysis on traditional face-to-face interventions for work-related stress yielded an overall combined effect size of d=.34, whereby the results for web-based stress-management interventions are mixed, ranging from non-significant [17] to moderate effect sizes [16]. Therefore, we aim for an effect size of d=.35.

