### Strengths

A major strength of the current study is the robust randomized controlled trial design, which is the gold standard for clinical trials. Furthermore, this is the first study in Germany to examine the efficacy and cost-effectiveness of a web-based stress-management intervention. We also include a large number of participants in this study to ensure sufficient power.

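### The 80% power stated for the intention-to-treat analysis is a complete-data figure: 264 randomised leaves practically no allowance for missing outcomes, and no correlation is given that could offset the loss

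*Protocol article*

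**What the plan says.** The Sample size section of the protocol article states: "We aim to include 264 participants to produce a statistically relevant effect size of d = .35, a power (1-β) of 80" per cent. The same sentence ties the figure to "an alpha of .05 (two-tailed test) for intention-to-treat analysis using PASS 12". The Abstract repeats it: "Based on a power calculation of d=.35 (1-β of 80%, α = .05), 264 participants will be recruited". The Randomization section uses the same number for allocation, "allocate participants (N=264) into each group at a ratio of 1:1", so 264 is the number randomised and not a number evaluable after loss.

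The Clinical analyses section makes intention-to-treat the main analysis, refers to standard missing-data references for handling missing values, and adds completers-only and per-protocol analyses. Its test for the primary outcome is a repeated-measures analysis of variance. The Aims section frames the primary hypothesis as a larger reduction in perceived stress from pre-test to post-test. The article gives no expected loss, no pre-post correlation, and does not name the test behind the 264. Under Strengths it says: "We also include a large number of participants in this study to ensure sufficient power".

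**The concern.** The power is stated for an intention-to-treat analysis without any condition on how many outcomes are observed. Intention-to-treat decides who is analysed and in which arm. It does not restore information about outcomes that nobody recorded. Imputation or likelihood methods can remove bias under their assumptions and can use a participant's other observed visits, but they do not bring the sample back to 264 complete outcomes.

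The outcomes are online self-reports at seven weeks and six months, and the plan itself provides for missing data. If some are missing and the primary test gains nothing from the baseline score, actual power is below the stated figure. A null result would then be read as coming from a trial with 80% power for d = .35 when it may have had noticeably less, and the Strengths section would support that reading.

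**Working it through.** **Inputs.** From Sample size: total N = 264, d = .35, power 80%, two-sided alpha .05. From Randomization: 1:1, so 132 per arm. Assumed, because the article gives neither: the proportion of missing outcomes (5 to 30%) and the pre-post correlation r (.4 to .6).

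**1. Reproducing 264.** The normal approximation gives n per arm = 2(1.960 + 0.842)² / 0.35² = 15.70 / 0.1225 = 128.1, so 129 per arm and 258 in total. The noncentral t gives 129.11, so 130 per arm and 260 in total. Power by the noncentral t is 79.97% at 129 per arm, 80.3% at 130 and 80.9% at 132. The figure therefore reproduces as a complete-data size for an unadjusted two-group comparison, with 264 − 260 = 4 participants to spare (4/264 = 1.5%).

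**2. Outcome data needed for 80%, unadjusted.** In whole participants 260/264 = 98.5%. Without rounding, 2 × 129.11/264 = 97.8%. So about 98%. The slope is shallow: power falls below 78% only when more than about 7% are missing (122.84/132 = 93.1% retained).

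**3. Power under assumed loss, unadjusted.** Effective n per arm = 132 × (1 − loss).

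| Missing | n per arm | Power at d = .35 | Detectable d at 80% |
|---|---|---|---|
| 0% | 132.0 | 80.9% | .346 |
| 5% | 125.4 | 78.8% | .355 |
| 10% | 118.8 | 76.6% | .365 |
| 20% | 105.6 | 71.6% | .387 |
| 30% | 92.4 | 65.8% | .414 |

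This is a worst case, since it counts each missing outcome as a full loss.

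**4. Group-by-time test.** With two time points, the group-by-time term of a repeated-measures analysis of variance is a t-test on change scores. If d is on the raw-score SD, the variance factor is 2(1 − r) and the effective d is .35/√(2(1 − r)).

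- r = .4: .35/√1.2 = .320; power 73.4% with complete data, 63.7% at 20% loss.
- r = .5: factor 1; identical to the unadjusted test (80.9% and 71.6%).
- r = .6: .35/√0.8 = .391; 88.6% and 80.8%.

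The break-even is 129.11 × 2(1 − r) = 132, so r ≈ .49. Below that, even complete data do not reach 80%.

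**5. Baseline as covariate (ANCOVA).** The variance factor is 1 − r² and the effective d is .35/√(1 − r²).

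- r = .4: .35/√0.84 = .382; power at 20% loss 78.9%; 80% power needs about 82% of outcomes.
- r = .5: .35/√0.75 = .404; power at 20% loss 83.2%; 80% power needs about 73% of outcomes.

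**The case against.** The best reply is that nothing stated is wrong. The number reproduces, the loss rates are assumed, and the planned test is not an unadjusted t-test on the post-test score, so the 98% threshold need not apply to it. With baseline as a covariate and r of .4 to .5, the design tolerates roughly 18 to 27% missing. The linear discount is also harsh, because the PSS-10 is collected at several visits in both arms and a participant missing one visit still contributes. Finally, a condensed article may leave an attrition allowance to the full protocol.

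Much of this stands, and it rules out several stronger readings:

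- A reader might infer that 264 is miscalculated. It is not; step 1 reproduces it.
- A reader might infer that the 80% is false under any realistic loss. The article gives neither the loss rate nor the correlation needed to say so, and a baseline-adjusted model could hold 80% under moderate loss.
- A reader might take the eCoach reminders and the dropout-reasons questionnaire as evidence that outcome data will be lost. The reminders concern unfinished training sessions, and the questionnaire is given to the intervention group only; both fit leaving the training. The missing-data provision in Clinical analyses is what bears on outcomes.
- A reader might object that d = .35 exceeds the meta-analytic .34. The gap is trivial, and the article also cites larger effects for web-based and two-component programmes.

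Two parts do not stand. The article names repeated-measures analysis of variance and not ANCOVA, and the group-by-time test gains only above r of about .5, so an unstated correlation cannot be counted in the plan's favour. And the point is not that an allowance goes unmentioned: a specific power is stated for intention-to-treat with 264 as the number randomised, and that pair leaves room for four missing outcomes.

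**Conclusion.** The concern holds in a limited form. N = 264 is a correct complete-data size, but the article attaches its 80% to an intention-to-treat analysis of 264 randomised participants while planning for missing data. As written, that figure is supported only by near-complete outcomes (about 98% for the unadjusted comparison) or by a pre-post correlation the article does not state.

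The size depends on both unknowns. Unadjusted, the shortfall is about 1 point at 5% loss, 3 at 10%, 8 at 20% and 14 at 30%, as an upper bound. For a group-by-time test it is larger if r is below about .5 and smaller above. For a baseline-adjusted analysis at r of .4 to .5 there is essentially no shortfall up to 20% loss. This is a fault in how the power is stated, not a calculation error, and it does not show that the trial is underpowered.

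**What to change.** Keep N = 264.

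1. In Sample size and the Abstract, restate the figure as about 81% power for d = .35 with complete outcome data (two-sample t-test, two-sided alpha .05).
2. Add the expected proportion of missing outcomes, and give power and detectable d at that proportion for the named primary model with its assumed pre-post correlation. For the unadjusted comparison, the detectable d is about .365 at 10% loss and .387 at 20%.
3. Preferably make baseline PSS-10 a covariate in the primary model, and say so in Clinical analyses, since that section now names repeated-measures analysis of variance only. At 20% loss the detectable d would then be about .387 × √0.84 = .355 for r = .4, or .387 × √0.75 = .335 for r = .5. If the group-by-time test is kept, state r and base the power on it.
4. Qualify the Strengths sentence so that sufficient power is tied to the stated loss and model.

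The cost is rewording in three places and, if item 3 is adopted, one explicit change to the primary model. No extra participants are needed. The quoted power may become less favourable, depending on the expected loss and the model.

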### Intervention

The web-based GET.ON Stress intervention is based on two main components: problem solving and emotion regulation. The intervention consists of seven sessions composed of modules for psycho-education (session 1), problem solving (sessions 2–3), emotion regulation (sessions 4–6) and plan for the future (session 7) (see Table 1). Each session can be completed in approximately 45–60 minutes and consists of general information, examples related to work, interactive exercises, quizzes, audio and video files, and downloadable work sheets and mp3 files. We will recommend to log in once or twice a week and to fill out a short daily stress diary. Depending on the module, further homework will be assigned. Using responsive web-design, participants can follow the program on the internet, a tablet or mobile phone. An integrated read-aloud function allows participants to follow the lessons in an audio-narrated way.

**Table 1 T1:** Content of the GET.ON stress training

**Session**	**Intervention content**	
1	Psycho-education	
2	Problem solving I	(Learning Phase)
3	Problem solving II	(Maintenance Phase)
4	Emotion regulation I	(Muscle- and breathing relaxation)
5	Emotion regulation II	(Acceptance and tolerance of emotions)
6	Emotion regulation III	(Effective self-support in difficult situations)
7	Plan for the future	

